| Secondary Analyses     | 
Comparison between active treatment and control arms relating to;
 
 
i] URTI-related relapse rate.
 
ii] Overall relapse rate (i.e. URTI related relapses plus non-URTl related relapses).
 
iii] Cumulative dose of prednisolone received.
 
iv] Proportion of subjects who develop, and severity of, steroid-related adverse events including behavioural problems.
 
v] Proportion of subjects who undergo both escalation and reduction of immunosuppressive therapy.
 
vi] Economic evaluation of cost per relapse and cost per QALY gained.
 
                                                                                                                                                                                                                                                                                                                                                                 |
| Exploratory Objectives | 
A single 10ml sample of blood will be collected for DNA and RNA extraction. This will be divided into two 5ml portions and used to
 
 
i] Perform a genome wide association study to look for possible genetic loci associated with steroid sensitive nephrotic syndrome (in collaboration with [name] and [name], Great Ormond Street Hospital and Institute of Child Health, University College, London)
 
ii] Perform whole exome screening, initially looking for the 22 genetic mutations known to date to be associated with nephrotic syndrome, then moving to the 4000 genes expressed in the podocyte (key cell within the kidney filter) and finally to the entire exome. RNA will be used to perform functional studies to ascertain whether any detected mutation is pathogenic (in collaboration with [name] and [name], Kings College London and University of Bristol)
 
 |

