#### 4.24 Monitoring of prednisolone related adverse effects

We will carefully monitor study subjects for prednisolone related adverse effects (see Appendix 2). As this is a Clinical Trial of an Investigational Medicine Product, we in any case need to document all adverse health events, their treatments and outcomes. Additionally to ensure that all adverse effects are recorded we will measure the following:

- i. Height will be carefully monitored at each study visit (with the exception of telephone or home study visits) using a calibrated stadiometer with the subject in bare or stocking feet.
- ii. Weight will be assessed at each study visit using calibrated scales.
- iii. Body mass index standard deviation score will be calculated from i] and ii].
- iv. Cushingoid features and hypertrichosis will be assessed by the clinician on a Likert scale and appetite will be assessed by the parent on a Likert scale.
- v. The presence or absence of striae will be documented at each study visit.
- vi. Behaviour will be assessed using the Achenbach Child Behaviour Checklist.
- vii. Blood pressure will be assessed at each study visit to document the incidence of hypertension.
- viii. Dipstick analysis of the urine will be performed at each study visit to look for glycosuria (**>5mmol/l**); where this is significant and persistent, plasma glucose will be measured in keeping with routine clinical practice.
- ix. The development of significant bacterial, viral and fungal infections will be documented.
- x. Use of varicella prophylaxis (zoster immune globulin or antiviral therapy) will be recorded.
- xi. We will prospectively collect information regarding all episodes of consultation with General Practitioners or hospital medical teams, including data on treatments prescribed or purchased. This will be incorporated into the costs measured as part of the health economic analysis.

If any of the above prednisolone related adverse-effects meet the criteria of an SAE the event must be recorded on the SAE form and faxed to the BCTU on [name] within 24 hours of the research staff becoming aware of the event. Please try to ensure that the local Principal Investigator has assigned causality to the SAE before reporting.

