The secondary endpoints include both continuous and categorical data items. The dichotomous data (e.g. incidence of escalation of background immunosuppressive therapy) will be analysed as per the primary outcome. Continuous data (e.g. prednisolone dose, quality of life scores) will be expressed as means and standard deviations, with differences in means and 95% confidence intervals. Longitudinal plots of the data over time will be constructed for visual presentation of the data. Data will be analysed using mixed effect repeated measures models with the interventions specified as independent variables. Baseline data will be included in the model as a covariate.

Analyses will be of all randomised subjects using intention to treat, except for those who do not have an URTI following randomisation. Over the course of the study up to the 12th July 2016, the number of patients who have completed the trial without experiencing at least one URTI is approximately 24% which is higher than the originally estimated <10% at the start of the trial. Exclusion of these subjects will result in no bias as these drop-outs are not related to the treatment and should by chance be equally distributed across the two treatment arms (this will be monitored throughout the trial). Sensitivity analyses will be performed on the 12 month data analyses due to the issues raised above. These analyses will be fully outlined in the Statistical Analysis Plan, and will include analyses with subjects censored at point of treatment escalation.

The only subgroup analyses planned are by the background treatment regimen that the subjects are on at randomisation (no long-term treatment; on long term maintenance prednisolone therapy; on other immunosuppressant therapy with long term maintenance prednisolone therapy; on other immunosuppressant therapy without prednisolone); an analysis comparing those subjects on prednisolone versus those not on prednisolone; and an analysis comparing those subjects on other immunosuppressant therapy versus those not on other immunosuppressant therapy. The study is not powered to detect differences in treatment effect across these subgroups, so these analyses will be considered as hypothesis generating.

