| 4.4. Secondary outcome measures                                                                                                                                                                                                                                                                                                                                                                                                                                                                                                                                                                                                                                                                               |
| 
The secondary outcomes are as follows:
 
 
i. Rate of URTI-related relapse of nephrotic syndrome
 
ii. Rate of relapse (URTJ-related and non URTI-related) of nephrotic syndrome
 
iii. Cumulative dose of prednisolone (mg/kg and mg/m^2) received over the 12 month period
 
iv. Incidence of serious adverse events (SAEs)
 
v. Incidence of adverse effects of prednisolone including assessment of behaviour using the Achenbach Child Behaviour Checklist
 
vi. Incidence of escalation of background immunosuppressive therapy
 
vii. Incidence of reduction of background immunosuppressive therapy
 
 |

- viii. Quality of life using the PedsQL (0=worst, 100=best). See Section 9.4 for questionnaire scoring.
- ix. Cost per relapse of nephrotic syndrome
- x. Cost per QALY gained

The secondary outcomes measures ix and x relate to the health economic analysis and are not part of this SAP.

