### **9.6. Analysis methods – secondary outcomes**

The number of participants experiencing any relapse (i.e. both URTI-related and non URTI-related relapses), the number of participants having an escalation of background immunosuppressant therapy and the number of participants having a reduction of background immunosuppressant therapy will be presented and analysed as per the primary outcome measure.

The rate of URTI-related relapses and rate of any relapse will be presented in the first instance as numbers of participants who have a relapse with the respective percentage, and in the second instance as a median and IQR. An adjusted incidence rate ratio with 95% confidence interval will be estimated using a Poisson regression model. An offset for the length of time the participant was in the trial will be included in the model. Statistical significance of the treatment group parameter will be determined from the p-value generated by the model.

The cumulative dose of prednisolone received over the 12 month period will be presented as means with standard deviations and ranges. Adjusted mean differences along with 95% confidence intervals will be estimated using a linear regression model. Statistical significance of the treatment group parameter will be determined from the p-value generated by the model.

Adverse effect data will be tabulated at each time point (3, 6, 9 and 12 months) with statistical significance determined by a chi-squared or Fisher's exact test (as appropriate). We will also assess whether or not each adverse event occurred over the whole trial period by assessing all the 3, 6, 9 and 12 month data collectively.

Quality of life measures are taken at multiple time points, as is the Achenbach Behaviour Checklist Scores. Means and standard deviations will be summarised at each time point. Data will be analysed using mixed effect repeated measures models with the minimisation variable and the baseline questionnaire score included in the model as covariates. Time will be included as a continuous variable in the model. In the initial model, a treatment by time cross-term will be included in the model. If this is not significant, it will be considered that the treatment effect

is constant over time, and models without the treatment by time cross-term will be fitted. Adjusted mean differences between groups will be presented alongside the respective 95% confidence interval.

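### No planned test uses the order of the Likert grades for Cushingoid features, hypertrichosis and appetite, so the severity comparison in the protocol synopsis is not delivered for these three steroid effects

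*Combined protocol and SAP*

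**What the plan says.** **What is recorded.** Protocol section 4.24 states: "Cushingoid features and hypertrichosis will be assessed by the clinician on a Likert scale and appetite will be assessed by the parent on a Likert" rating. Height and weight are measured, and "Body mass index standard deviation score will be calculated from i] and ii" (the height and weight items). Striae are noted as present or absent, and blood pressure is taken in order to document how often hypertension occurs. The visit schedule in protocol section 4.12 places a steroid toxicity assessment at baseline and at months 3, 6, 9 and 12.

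**What is to be compared.** The protocol synopsis, under Secondary Analyses, lists "Proportion of subjects who develop, and severity of, steroid-related adverse events including behavioural problems". For continuous secondary data, protocol section 4.29 says: "Data will be analysed using mixed effect repeated measures models with the interventions specified as independent variables", with the baseline value as a covariate. The outcome in SAP section 4.4 is worded as "Incidence of adverse effects of prednisolone including assessment of behaviour using the Achenbach Child Behaviour Checklist".

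**What is planned.** SAP section 9.6 says "Adverse effect data will be tabulated at each time point (3, 6, 9 and 12 months) with statistical significance determined by a chi-squared or Fisher's" test, and then: "We will also assess whether or not each adverse event occurred over the whole trial period". The same section gives the Achenbach scores and quality of life a mixed repeated-measures model adjusted for baseline score and the minimisation variable. SAP section 9.7 gives only summary statistics to data that are not a pre-specified outcome.

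**The concern.** The synopsis separates two comparisons: how many children develop a steroid effect, and how severe it is. A Likert grade can answer the second. Neither method in SAP 9.6 does so for Cushingoid features, hypertrichosis or appetite. A chi-squared or Fisher test on a table of grades gives the same p-value if the grades are shuffled. An ever-occurred indicator counts mild and marked Cushingoid change alike. Height and BMI SDS have a related gap: no model is named for them, although the protocol's general rule for continuous secondary data would supply one.

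Reducing steroid adverse effects is secondary objective iv, and the research question in protocol section 3.2 asks about safety as well as effect. Protocol section 8 accepts that children may receive extra prednisolone without benefit. If the tests for visible steroid toxicity have low power, a non-significant result may be read as reassurance.

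**Working it through.** **1. Sample size.** The plan states no power for adverse effects, so its primary calculation supplies the number analysed. For 50% v 32.5%, 80% power, two-sided 5%:

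n per arm = [1.96√(2p̄q̄) + 0.8416√(p₁q₁ + p₂q₂)]² / (p₁ − p₂)²

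with p̄ = 0.4125, this is [1.3646 + 0.5766]² / 0.175² = 3.768/0.0306 = 123.04, so 124 per arm and 248 in total (plan: 250). Then 250/0.7 = 357.1, so 358 (plan: 360). The plan's figures reproduce. I use 125 per arm. If only the 24% without an URTI are lost, 360 × 0.76/2 is about 137 per arm, and the pattern below is the same.

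**2. Assumptions.** The documents give neither the number of grades, nor their distribution, nor an effect size. I assume 4 or 5 grades, 30-70% of controls in the lowest grade, and a common odds ratio (OR) towards higher grades in the active arm.

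**3. Worked example.** Controls 40/30/20/10%, OR 1.8. The control cumulative odds 0.667, 2.333 and 9 are divided by 1.8, giving 0.370, 1.296 and 5. The active-arm grades are therefore 27.0/29.4/26.9/16.7%.

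- *Unordered chi-squared, 3 df.* Noncentrality = 125 × Σ(p − q)²/(p + q) = 125 × (0.0251 + 0.0001 + 0.0101 + 0.0167) ≈ 6.5. Power about 55%.
- *Any/none, 1 df.* Noncentrality = 125 × (0.130²/0.670 + 0.130²/1.330) ≈ 4.7. Power about 58%.
- *Ordinal (proportional odds).* Information = (250/12)(1 − Σp̄³) = 20.83 × (1 − 0.079) = 19.2. z = ln 1.8 × √19.2 = 0.588 × 4.38 = 2.57. Power = Φ(2.57 − 1.96), about 73%.

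Simulation of the same case gave 55%, 58% and 72%, with the Wilcoxon-Mann-Whitney test as the unadjusted ordinal analysis.

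**4. Ranges at 125 per arm (simulated).**

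| Common OR | Unordered chi-squared | Ordinal test |
|---|---|---|
| 1.5 | 22-28% | 35-44% |
| 1.8 | 45-55% | 62-73% |
| 2.0 | 60-71% | 77-87% |

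The gain over the unordered test is roughly 11 to 23 points across these scenarios.

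**5. Against any/none, OR 1.8.** The gain depends on how many children sit in the lowest grade:

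- 80%, 85% or 90% in the lowest grade: 52 v 53%, 44 v 45% and 34 v 35%, so about 1 point.
- Three grades at 60/30/10%: about 4 points.
- 70% in the lowest of four grades: about 3 points.
- 40/30/20/10%: 72 − 58 = 14 points.
- 30% in the lowest of five grades: over 20 points.

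Each simulation represents one assessment, such as a single visit or the worst grade. It does not model four repeated visits or adjustment for baseline grade.

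**The case against.** The best defence is that the SAP matches the outcome as defined. The objective speaks of incidence and prevalence, and the outcome of incidence. A table at each visit gives prevalence and an ever-occurred table gives incidence. Severity as a compared quantity appears only in the synopsis line. The per-visit table may well show every grade, so severity could be described by arm. This stands as a reason to keep the tables. It does not supply a test that uses grade order, and the synopsis line remains unmet for the three items.

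A second defence is that the size is unknown. If most children have no visible effect, any/none loses almost nothing. That also stands for the ever-occurred assessment. The loss against an unordered test on the full table persists, but it applies only if the full table is what gets tested, and the SAP does not say.

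A third is that each effect is tested at four visits and overall with no multiplicity correction, so some positive signal is more likely than one test suggests. This is true, but several unadjusted looks are a poor substitute for one comparison of severity.

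A reader might also infer that all steroid harm is tested only as categories. The documents do not support this: behaviour belongs to the same outcome and is modelled on its full scale, and striae are genuinely binary. Nor does the point extend to blood pressure, whose stated purpose is the incidence of hypertension.

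**Conclusion.** The point holds for Cushingoid features, hypertrichosis and appetite. They are graded at every visit and the synopsis promises a severity comparison, but SAP 9.6 plans no test that uses the grade order. At 125 per arm and an assumed common OR of 1.8, an ordinal test has 62-73% power where the unordered chi-squared test has about 45-55%. The gain over any/none is anywhere from about 1 point to over 20. The direction is secure under a shift towards higher grades. The size rests on distributions and effects that the documents do not give.

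For height and BMI SDS the finding is smaller: the SAP names no comparison. A reader might infer that they will be cut into categories, with a matching loss of power. No section says so, and they may simply be summarised under SAP 9.7, so no power figure is attached to them here.

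It would also go too far to say that the severity comparison is missing altogether, since the behavioural part is delivered through the Achenbach model. This is a worthwhile, inexpensive improvement to a secondary safety analysis. It does not affect the primary outcome.

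**What to change.** In SAP section 9.6:

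1. Analyse Cushingoid features, hypertrichosis and appetite on their full grade with a proportional-odds model, either repeated measures over months 3 to 12 or on the worst post-randomisation grade. Choose one in advance. Adjust for baseline grade and the minimisation variable, and report a common odds ratio with 95% CI. This also meets the adjustment rule for all outcomes in SAP section 9.1, which a chi-squared or Fisher test does not.
2. Analyse height and BMI SDS with the baseline-adjusted mixed model already specified for PedsQL and Achenbach, in line with protocol section 4.29.
3. Keep the per-visit and ever-occurred tables for prevalence and incidence, and keep chi-squared or Fisher tests for binary items such as striae.
4. State how many grades each Likert item has and whether the per-visit table shows them all.

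The cost is SAP wording and a few models on data already collected. The drawbacks are that the model relies on approximately proportional odds, and that a common odds ratio is less familiar to clinicians than a percentage. Showing the retained tables beside it limits the second.

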#### **4.21 Study visits**

At the baseline visit:

- Confirmation of inclusion and exclusion criteria.
- Informed consent/assent.
- Randomisation and allocation of study number.

- Information will be captured on dates of last two relapses.
- Medical and drug history since diagnosis of nephrotic syndrome.
- A physical examination will be performed, including measurement of height, weight and blood pressure.
- Calculation of dose of study drug to be administered when URTI occurs and provision of written information for parents regarding this.
- Scoring of prednisolone adverse effects will be performed by use of a standardised proforma.
- In order to evaluate changes in subject behaviour associated with the different prednisolone regimens, the Achenbach Child Behaviour Checklist (ACBC) will be used. The ACBC is a standardised measure made up of 120 items measuring internalising (withdrawn, somatic complaints, anxiety/depression, thought problems) and externalising (social problems, attention problems, delinquent and aggressive) behaviour problems. A total Behavioural Problem score is calculated from these problem scales and forms the basis of comparison with age and gender-matched normative data.
- Information relating to quality of life will also be collected using the CHU-9D and EQ-5D (dependent upon subject age) and PedsQL questionnaires.

At subsequent study visits (months 3, 6, 9 and 12):

- Details will be collected about any URTI that has developed and whether study drug has been commenced.
- Information will be captured regarding recent history of relapse and any treatment received for this.
- Recent other medical/drug history will be recorded.
- Adverse events will be documented.
- A study drug compliance check will be performed (tablet count using counting triangle).
- A physical examination will be performed, including measurement of height, weight and blood pressure.
- Scoring of prednisolone adverse effects will be performed by use of a standardised proforma.
- Recalculation of dose of study drug to be administered when URTI occurs and provision of written information for parents regarding this.
- If 3 or more courses of study drug have been administered since previous visit, confirmation of parental understanding of definition of URTI.
- Information will be collected about consultations with health care professionals in primary care (including the home) and also in hospital (both outpatient and inpatient) and any treatment administered.

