## **5.3. Analysis populations**

All primary analyses (primary and secondary outcomes including safety outcomes) will be based on the intention-to-treat (ITT) principle. Participants will be analysed in the intervention group to which they were randomised, and all participants shall be included whether or not they

received the allocated intervention following an URTI. This is to avoid any potential bias in the analysis.

The ITT population will not include all of the randomised population. Analyses will be based on a modified ITT population which will include only those participants who had an URTI over the 12 month follow up period. Excluding those participants who did not have an URTI will result in no bias as taking the study medication is conditional on them experiencing an URTI, and this should by chance be balanced between the two groups.

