## **9. Analysis methods**

### **9.1. Covariate adjustment**

In the first instance, intervention effects between groups for all outcomes will be adjusted for the minimisation parameter listed in section 4.6. Other covariate adjustment will be baseline values for parameters where available (e.g. an analysis of questionnaire scores will also include the baseline score as a covariate in the model).

If covariate adjustment is not possible (e.g. the model does not converge), the minimisation variable covariate will be removed from the model, but where applicable adjustment for baseline values will still be made. If the model still does not converge, unadjusted estimates will be produced, and it will be made clear in the final report why this occurred (e.g. not possible due to low event rate/lack of model convergence).

If the log-binomial model fails to converge, a Poisson regression model with robust standard errors will be used to estimate the same parameters. If this also fails to converge, unadjusted estimates will be produced from the log-binomial model. It will be made clear in the final report why this occurred (e.g. not possible due to low event rate/lack of model convergence).

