### **9.8. Safety data**

The number and percentage of participants experiencing any adverse events, serious adverse events (SAEs) and suspected unexpected serious adverse reactions (SUSARs) will be presented by intervention group. Statistical significance will be determined by a chi-squared or Fisher's exact test (as appropriate). A table listing the SAEs including information on the nature of the event and whether or not it was deemed related to the trial treatment will be provided.

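### SAP 9.6 and 9.8 test steroid adverse effects without the adjustment SAP 9.1 requires for all outcomes, and the whole-period flag has no rule for effects already present at entry

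*Combined protocol and SAP*

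**What the plan says.** SAP 9.6, on the effects recorded at the follow-up visits: "Adverse effect data will be tabulated at each time point (3, 6, 9 and 12 months) with statistical significance determined by a chi-squared" test, with Fisher's as the alternative. It adds a summary over follow-up: "We will also assess whether or not each adverse event occurred over the whole trial period", using the month 3, 6, 9 and 12 data together. SAP 9.8, on adverse events, SAEs and SUSARs: "Statistical significance will be determined by a chi-squared or Fisher's exact test (as appropriate"). Neither section names a covariate, an effect estimate or a confidence interval for these data.

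SAP 9.1 sets the general rule: "In the first instance, intervention effects between groups for all outcomes will be adjusted for the minimisation parameter listed in section 4.6". It continues: "Other covariate adjustment will be baseline values for parameters where available". SAP 4.4 lists both SAEs and prednisolone adverse effects among the secondary outcomes, so the rule covers them.

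Baseline data exist. Protocol 4.21 has, at the baseline visit and again at each follow-up visit: "Scoring of prednisolone adverse effects will be performed by use of a standardised proforma". Protocol 4.24 puts Cushingoid features, hypertrichosis and appetite on Likert scales.

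On population, SAP 5.3 applies to safety outcomes as well as efficacy "a modified ITT population which will include only those participants who had an URTI over the 12 month follow up period".

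**The concern.** Two sections of one SAP give different analyses for the same outcomes. Other binary secondary outcomes (escalation and reduction of background therapy) follow the primary-outcome model, with adjusted risk difference and relative risk. Adverse effects are left out of that without a stated reason.

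The omission of baseline matters in this population. Entry requires at least two relapses in the past year, and protocol section 8 says these children will already be receiving substantial yearly amounts of prednisolone. Some will therefore have steroid features when randomised. If such a feature persists, the month 3 to 12 data will show it in both arms whatever the study drug does. The protocol synopsis asks for the proportion who develop steroid-related events, and for their severity. A flag that cannot tell a new feature from an old one does not answer the first part, and tests of occurrence do not use the Likert grades for the second.

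Whether the intervention increases steroid toxicity is one of the open questions that protocol section 1 gives as a reason for the trial. A comparison with avoidably low power could be read as reassurance.

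**Working it through.** **The texts side by side.** SAP 9.1: all outcomes, adjusted for regimen and for baseline where available. SAP 9.6 on Achenbach and quality of life: a mixed model with baseline score and regimen, consistent with 9.1. SAP 9.6 on the remaining adverse effects, and 9.8: a test with no covariates, inconsistent with 9.1. Protocol 5.1 does not count a pre-existing condition as an adverse event unless it worsens significantly; nothing carries that rule into the proforma scores or the whole-period flag.

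**Sample size.** The documents give no figure for the adverse-effect comparison. The primary calculation reproduces: with n = [1.96√(2p̄q̄) + 0.8416√(p₁q₁ + p₂q₂)]² / (p₁ − p₂)², 0.50 v 0.325 gives 124 per arm, or 248 (stated 250); 250/0.70 = 357.1, so 358, rounded to 360. Protocol 4.29 reports that about 24% of completers had no URTI, so the analysed population is about 180 × 0.76 = 136.8, or 137 per arm, before other losses.

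**Ignoring baseline status.** The rates are assumptions. Let b be the share affected at entry. Among children free of the effect, new onset is 15% (control) v 30% (active). Among those affected, 70% or 95% stay affected in either arm. The crude difference is then (1 − b) × (0.30 − 0.15). Power is from simulation with 137 per arm and 1,500 runs per scenario (Monte Carlo standard error at most √(0.25/1500) = 0.013). The stratified test is Mantel-Haenszel by baseline status. Paired entries are for 70% / 95% persistence.

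| b | Crude difference | Unadjusted | Stratified | New onset only | Loss v stratified (points) |
|---|---|---|---|---|---|
| 0% | 0.150 | 0.868 / 0.851 | 0.867 / 0.848 | 0.868 / 0.851 | none |
| 10% | 0.135 | 0.715 / 0.694 | 0.760 / 0.802 | 0.813 / 0.813 | 4.5 / 10.8 |
| 20% | 0.120 | 0.561 / 0.544 | 0.661 / 0.728 | 0.782 / 0.754 | 10.0 / 18.4 |
| 30% | 0.105 | 0.439 / 0.420 | 0.519 / 0.674 | 0.713 / 0.734 | 8.0 / 25.4 |
| 40% | 0.090 | 0.333 / 0.314 | 0.406 / 0.560 | 0.657 / 0.633 | 7.3 / 24.6 |

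With no drug effect (20% new onset in both arms, 90% persistence, 4,000 runs), the unadjusted test rejected in 0.044 of runs at b = 20% and again at b = 40%.

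**The URTI restriction.** Assume children without an URTI, who are due no study drug, have the control rate. Among all randomised, the difference is then 0.76 times that in children with an URTI. Power = Φ{[|p₁ − p₂|√n − 1.96√(2p̄q̄)] / √(p₁q₁ + p₂q₂)}.

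| Assumed rates | URTI only, 137 per arm | All randomised, 180 per arm |
|---|---|---|
| 10% v 20% | 0.641 | 0.552 (difference 7.6 points) |
| 20% v 30% | 0.480 | 0.394 (7.6 points) |
| 30% v 45% | 0.730 | 0.618 (11.4 points) |

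The restriction gains about 9 to 11 points of power.

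**The case against.** - *Behaviour is already handled.* Correct. The Achenbach score is the one measure named within the adverse-effect outcome, and it is adjusted for baseline and regimen. The point is confined to the other effects.
- *Protocol 5.1 already removes pre-existing conditions, and the SAP is to be read with the protocol.* This carries weight. A reader might infer that features present at entry will certainly be counted as trial events; the documents do not establish that. They leave it open, because the proforma is scored afresh at each visit and no SAP rule links those scores to 5.1.
- *Prevalence is a stated objective.* It is (SAP section 3), and visit-wise tables serve it. They should stay. Prevalence and new onset are different quantities, so the smaller crude contrast is not a biased estimate of the larger.
- *The power figures are assumed.* They are. The documents give no adverse-effect rates, and the loss vanishes if nobody is affected at entry.
- *Adjustment may fail for sparse events.* SAP 9.1 already allows unadjusted estimates in that case, and exact tests suit rare SAEs.
- *The population rule.* A reader might infer that analysing only children with an URTI hides or dilutes toxicity. The direction is the opposite: those excluded are due no study drug, and adding them shrinks the contrast. Nor do the documents show that any of the roughly 24% took study drug. Parents are asked to contact the site before or within 24 hours of starting it, and all reported adverse-event data go to the DMEC. What remains is completeness. Parents start treatment on their own judgement of the criteria, SAP 9.10 allows that some URTIs may go unreported, and its check of the excluded children covers relapses only.

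**Conclusion.** The contradiction between SAP 9.1 and SAP 9.6/9.8 is plain on the text, and so is the missing rule for effects present at entry. The consequence is reduced power and precision for proforma steroid effects other than Achenbach behaviour. There is no inflation of type I error, so the plan does not create false safety signals.

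On the assumed rates, the loss against a baseline-stratified test is roughly 5 to 25 power points for 10 to 40% affected at entry. This rests on a doubling of new onset, no drug effect on existing features, and 70 or 95% persistence. It takes in baseline status only; any further gain from adjusting for regimen was not calculated.

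The URTI population is sound for the treatment comparison. The safety gap is limited to events in excluded children, including any who took study drug without a recorded URTI; the documents do not say whether there were any.

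**What to change.** 1. Reconcile SAP 9.6 and 9.8 with 9.1. For each adverse effect, report a risk difference or relative risk with 95% CI, adjusted for baseline status and background regimen, using the binomial models and fallback rules the SAP already has. SAEs and SUSARs have no baseline score, so regimen alone applies. Use an ordinal model for Likert items and keep Fisher's exact test for rare events.
2. Define the whole-period flag as new onset or worsening from the baseline score, and cite protocol 5.1.
3. Keep the month 3, 6, 9 and 12 tables, with baseline alongside, as descriptive prevalence without tests.
4. Keep the URTI population for the between-group comparison. Add AEs, SAEs and SUSARs for every child who took at least one study tablet, and an all-randomised listing for completeness.

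The cost is SAP wording and modest programming. The baseline scores are already collected. Sparse outcomes may end in the exact-test fallback, and the ordinal models give odds ratios where the SAP otherwise uses risk differences and relative risks.
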